## Abstract

**Background:**

Intimate partner violence (IPV) threatens the safety and health of women worldwide. Safety planning is a widely recommended, evidence-based intervention for women experiencing IPV, yet fewer than 1 in 5 Canadian women access safety planning through domestic violence services. Rural, Indigenous, racialized, and immigrant women, those who prioritize their privacy, and/or women who have partners other than men, face unique safety risks and access barriers. Online IPV interventions tailored to the unique features of women’s lives, and to maximize choice and control, have potential to reduce access barriers, and improve fit and inclusiveness, maximizing effectiveness of these interventions for diverse groups.

**Methods/Design:**

In this double blind randomized controlled trial, 450 Canadian women who have experienced IPV in the previous 6 months will be randomized to either a tailored, interactive online safety and health intervention (i*CAN Plan 4 Safety*) or general online safety information (usual care). *iCAN* engages women in activities designed to increase their awareness of safety risks, reflect on their plans for their relationships and priorities, and create a personalize action plan of strategies and resources for addressing their safety and health concerns. Self-reported outcome measures will be collected at baseline and 3, 6, and 12 months post-baseline. Primary outcomes are depressive symptoms (Center for Epidemiological Studies Depression Scale, Revised) and PTSD Symptoms (PTSD Checklist, Civilian Version). Secondary outcomes include helpful safety actions, safety planning self-efficacy, mastery, and decisional conflict. In-depth qualitative interviews with approximately 60 women who have completed the trial and website utilization data will be used to explore women’s engagement with the intervention and processes of change.

**Discussion:**

This trial will contribute timely evidence about the effectiveness of online safety and health interventions appropriate for diverse life contexts. If effective*, iCAN* could be readily adopted by health and social services and/or accessed by women to work through options independently. This study will produce contextualized knowledge about how women engage with the intervention; its strengths and weaknesses; whether specific groups benefit more than others; and the processes explaining any positive outcomes. Such information is critical for effective scale up of any complex intervention.

**Trial registration:**

Clinicaltrials.gov ID NCT02258841 (Registered on Oct 2, 2014).

## Background

Intimate partner violence (IPV), a pattern of physical, sexual and/or emotional abuse in the context of coercive control [1], affects 1 in 3 Canadian women in their lifetimes [2] and often persists even after separation [3]. Over time, chronic stress and fear associated with experiencing IPV contributes to depression, anxiety, and Post-Traumatic Stress Disorder(PTSD) [4, 5]. In a meta-analysis of studies of female IPV victims, the mean prevalence of depression was estimated at 47.6%, and of PTSD at 63.8% (three- to five-fold and five-fold increases over general female population rates, respectively) [4].

Recognizing that a relationship is abusive and sorting out what to do about it is often a long, complex process during which women learn by trial and error about the risks to their physical and emotional safety and health, the resources and supports available to them, and the consequences of various strategies [6, 7]. Women’s capacity to address their safety is intertwined with their health. For example, women with poorer mental health are more likely to return to an abusive partner after initially separating [8]. To improve the mental health and quality of life of women experiencing IPV, gender- and context-specific, culturally safe interventions are urgently needed.

However, few interventions have been shown to improve the safety, health or quality of life of women experiencing IPV. Safety planning, including education to increase women’s awareness about IPV, and personalized support to identify options for reducing risks and support for accessing resources, is one of the most widely recommended IPV interventions [9]. There is evidence from systematic reviews that providing information and support to engage women in safety planning and accessing services that meet their needs reduces both physical and psychological violence [9, 10], but the effects on women’s mental health and well-being are unknown. Although violence-specific services are a key source of help with safety planning, fewer than 1 in 5 Canadian women who experience IPV access such services [11]. Rural, Aboriginal, racialized and immigrant women, women with partners other than men, and those who prioritize privacy (including more affluent women) face unique safety risks and barriers to accessing information and support for safety planning [12–15]. Effective, accessible, personalized interventions are needed to support women’s capacity to engage in actions to promote their safety and well-being, and potentially, to improve their sense of confidence, control and mental health.

Effective online health interventions have been developed in varied domains, including smoking cessation, depression, anxiety and sexual health [16–18]. Evidence shows that interaction, feedback, and tailoring are important features of these online interventions [17]. For women experiencing IPV, personalized, online interventions could improve access to information and support for safety planning and well-being, particularly for women who are reluctant or unable to access formal resources. In a recent pilot test of the first interactive, online safety decision aid for women experiencing IPV, called IRIS, Glass, Eden, Bloom and Perrin [19] found that women’s safety planning increased and decisional conflict decreased immediately after one use of this resource. The effectiveness of IRIS in improving the mental health of women exposed to IPV was recently tested in a randomized controlled trial in the United States [20], the results of which are pending. Two other variations of this online intervention (isafe and I-DECIDE) are currently being tested in randomized controlled trials in New Zealand [21] and Australia [22].

Drawing on these online interventions and our longstanding history of conducting research with women who have experienced IPV, we developed an evidence-based online safety and health intervention for diverse Canadian women experiencing IPV, called ‘*iCAN Plan 4 Safety’ (*hereafter referred to as *iCAN)*. In the development phase, we drew on insights from our completed research examining women’s lives and health after separation from abusive partner [23–27], including research to develop and test a complex health promotion intervention (called iHEAL) designed to support health and quality of life of women transitioning out of an abusive relationship [28, 29], and current research testing an adaptation of iHEAL for Indigenous women with histories of IPV [30]. In developing the intervention, we drew on these studies, our theoretical grounding and current literature to: a) broaden the concept of women’s safety, shifting beyond a focus on immediate physical risks to emphasize safety as an ongoing issue for women (including after separation), especially emotional safety, and a variety of issues that are closely linked to safety concerns, including women’s health and well-being over time; b) focus on developing a personalized (tailored) intervention that would be inclusive of and ‘fit’ with the uniqueness and complexity of Canadian women’s lives, particularly those facing the most substantial barriers to support; c) adopt an approach that recognizes and further builds women’s strengths and capacities, including their awareness of their own priorities and risks; knowledge of a wide range of options for addressing safety, health and life concerns; and confidence in their ability to try out these actions, while keeping control and choice in women’s hands. During the development phase, the online intervention was refined by iteratively integrating feedback about both content and usability until it was deemed acceptable by potential end-users. In this paper, we describe the trial protocol for testing the effectiveness of our online safety and health intervention (*iCAN*) among Canadian women.

### Objectives of the trial

The primary aim of this study is to test the effectiveness of *iCAN,* a tailored, online safety and health intervention, in improving the health and safety actions of adult women experiencing IPV. A group of women completing *iCAN* will be compared to a control group who receive general online safety information as a proxy for usual care. We hypothesize that, compared to the control group, women in the intervention group will: 1) have reduced symptoms of depression and PTSD (primary outcomes), and increase self-efficacy for safety planning, use of helpful safety actions, and mastery (secondary outcomes) at 6 and 12 months post-baseline; and 2) reduced decisional conflict immediately post-baseline (after completing the intervention one time) and at 6 and 12 months post-baseline. Additional aims are to: a) describe how women engage with the intervention, and their perceptions of its strengths and weaknesses; b) examine whether repeat engagement or dose are related to intervention effects; c) explore whether specific groups of women benefit in more or different ways from the intervention than others; and, d) examine the processes of change that explain how any positive outcomes are achieved.

## Methods

### Trial design

A two arm, double-blind randomized controlled trial is being conducted to test the effectiveness of *iCAN* in a diverse sample of Canadian women who are experiencing IPV. The protocol was developed using CONSORT e-health guidelines [31]. Outcomes will be measured pre-intervention (baseline) and 3, 6 and 12 months post-intervention; decisional conflict will also be measured immediately post-intervention (after a single completion of the intervention). Website utilization data are being collected to capture access to and use of the intervention and control conditions. Women’s experiences of engaging with the intervention and control condition will be explored after completion of the 12-month study visit using their ratings of potential benefits and harms and comments about their experiences (collected online) and via in-depth qualitative interviews conducted with a sub-sample of approximately 60 women. Ethics approval for this study was obtained in July 2014 from the Institutional Research Ethics Boards at the University of Western Ontario, University of British Columbia, and University of New Brunswick.

### Participant inclusion criteria

The target population for this trial is English speaking women aged 19 years or older, living in the provinces of Ontario, New Brunswick, or British Columbia who self-identify as experiencing IPV (physical, sexual or emotional abuse within the context of coercive control) by a current or former partner (boyfriend, girlfriend, husband, wife, or intimate partner) in the previous 6 months. Exposure to IPV will be determined by a positive response to at least one question on a modified 4-item version of the Abuse Assessment Screen, a standardized IPV screening tool that has been used in both research and clinical settings [25, 32, 33]. Specifically, women will be asked whether, in the previous 6 months, a partner or ex-partner ever: a) hit, kicked or otherwise physically hurt her; b) forced her to have sexual activities against her will; c) did things to make her feel afraid of them; or d) did things to try and intimidate her or to control her thoughts, feelings or actions. Eligible participants must have access to a safe computer (to access the study website), safe email address (to which study-related information will be sent), and a safe mailing address (e.g., that of a friend or family member) to which the participation fee can be sent. Women not meeting all of these criteria will be excluded from participation.

### Recruitment

Women will be recruited to the trial using advertisements posted in a variety of online spaces (e.g., classified ads, health or violence websites, online discussion forums), supplemented by more traditional approaches to advertising in community settings (e.g., libraries), or through organizations, associations or service agencies accessed by women. Women seeking more information about the study will be directed to the study website (www.icanplan4safety.ca) or asked to contact a Research Assistant (RA) by email or a toll-free telephone number. This approach is similar to that utilized by the IRIS trial, and mirrors the varied ways that women might discover and access the online intervention outside of a research context.

### Number of participants required

A sample of 450 women (225 per group) will be recruited for this trial based on the statistical power needed to both test the impact of the tailored online intervention on primary outcomes using a general estimating equations (GEE) approach, and, subsequently, to examine mechanisms by which the intervention exerts its effects on these outcomes using Structural Equation Modeling (SEM). We based the power analysis on two key outcomes: decreased symptoms of depression, and of PTSD. Baseline means and standard deviations from the IRIS study [34], a similar trial in the USA, were used in the power analysis. In estimating the sample size, we varied the percent change over time in the intervention group relative to the control group from 15% to 20% which corresponds to moderate effects sizes, 0.29 and 0.52, found in previous studies of IPV interventions. The power analysis was based on repeated measures ANOVA since specific estimates of variance needed to calculate sample size for GEE are not available. However, in the GEE we will be able to retain all cases in the analysis, including those with missing data. With an alpha of .05, 15% greater change in the intervention group, relative to the control group, a sample size of 400 participants provides .73 power for depression and .92 power for PTSD. With a 20% greater change in the intervention, power is .94 for depression. We assume that attrition will be approximately 10%, based on the retention rate in the recently completed US trial (<10% at 12 month follow up) [35] and our recent success in retaining 81% of a cohort of women who had experienced IPV over a 4- year period. Attrition of 10% at 12 months would result in a final sample of 405 women, adequate for all analyses.

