### Statistical analysis

#### Examination of outcomes by study arm

The effectiveness of the intervention will be assessed by comparing the intervention and control groups on changes in outcome measures, between the baseline and the 3, 6, and 12 month post-baseline assessments. We will test the hypothesis that, at 3, 6 and 12 months post-baseline, the intervention group will have improved mental health (our primary outcomes), in comparison to the control group, using intent-to-treat principles with generalized estimating equations (GEE). The same approach will be used for testing secondary outcomes which hypothesize decreased decisional conflict, increased safety seeking behavior, mastery and self-efficacy. Separate analyses will be conducted for each outcome. The parameter of interest is the group (intervention vs. control) by time interaction, which if significant means that change over time differs for intervention and control groups. Significant findings will be graphed to determine the nature of the effect. Potential confounding variables for which intervention and control groups are significantly different at baseline and variables that are related to missingness will be entered in the model. These analyses will establish overall effect sizes, for specific outcomes, for the intervention.

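### Entering missingness predictors as GEE covariates does not protect the 12-month effect from dropout driven by earlier follow-up scores, and the rule does not confine those predictors to baseline variables

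*Protocol article*

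**What the plan says.** All references are to the protocol article.

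- Under *Examination of outcomes by study arm*, the arms are compared "using intent-to-treat principles with generalized estimating equations (GEE"). "The parameter of interest is the group (intervention vs. control) by time interaction", with visits at baseline, 3, 6 and 12 months.
- The same paragraph adds two kinds of covariate. The first is confounders that differ significantly between arms at baseline. The second is given as "variables that are related to missingness will be entered in the model". The baseline qualifier belongs to the first kind only.
- Under *Number of participants required*, power was computed by repeated measures ANOVA. The text then says: "However, in the GEE we will be able to retain all cases in the analysis, including those with missing data".
- The same section assumes about 10% attrition: "Attrition of 10% at 12 months would result in a final sample of 405 women, adequate for all analyses". As supporting evidence it cites "our recent success in retaining 81% of a cohort of women who had experienced IPV over a 4- year period".

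**The concern.** GEE uses every visit that a woman completes. That secures efficiency, but it does not by itself secure an unbiased effect. Without weights or imputation, GEE is guaranteed consistent only if missingness is completely at random or depends only on covariates in the mean model. A woman who stops because her 3- or 6-month symptoms are severe falls outside that guarantee. The planned remedy cannot bring her back in: her earlier scores are outcomes, and putting them on the right-hand side changes the effect being estimated.

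The rule is also open-ended. Site use, abuse severity, safety actions and mastery are all recorded after randomisation (*Trial process*, *Data collection*). Safety strategies, support, mastery and abuse severity are named as mediators under *Testing the mechanisms that explain the interventions effects*. If such a variable predicts missingness, a literal reading puts it in the primary model, where it could remove part of the effect and weaken the intention-to-treat comparison.

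At stake is the 12-month group-by-time effect. Stated power for depression is .73 at the smaller change considered, which leaves little room for attenuation.

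**Working it through.** **The plan's own figure.** 450 × (1 − 0.10) = 405, as stated. The cited cohort lost 100% − 81% = 19%, which serves here as a higher attrition scenario.

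**Inputs from the article.** Four visits; 1:1 allocation; about 10% attrition; effect 0.29, the smaller of the two effect sizes given.

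**Inputs assumed, because the article does not give them.** Outcome SD 1; within-woman correlation; dropout model; working correlation.

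**Quantity estimated.** With a saturated group-by-time mean, the 12-month effect is (mean at 12 months − mean at baseline) in the intervention arm minus the same difference in control. GEE solves Σ D′V⁻¹(y − μ) = 0 over observed visits. Under independence this reduces to observed means, so selection among women still in the study passes straight through. Under a non-trivial V, earlier visits partly correct for it.

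**Design A.** AR(1) correlation 0.6. Dropout occurs only between 6 and 12 months, with logit P(drop) = −2.3 + s × (6-month score), where s depends on the arm. True effect −0.29. Large-sample results:

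| Where symptoms drive dropout | Lost, control / intervention | Independence | Exchangeable | Unstructured |
|---|---|---|---|---|
| Both arms, s = 1 | 12% / 11% | −0.28 | −0.29 | −0.29 |
| Control only, s = 1 | 12% / 9% | −0.22 | −0.28 | −0.29 |
| Intervention only, s = 1 | 9% / 11% | −0.35 | −0.30 | −0.29 |
| Opposite, s = 1 and −1 | 12% / 14% | −0.15 | −0.26 | −0.28 |

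With the correct covariance, the estimate is −0.29 in every row.

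**Design B.** Dropout can occur at each visit and depends on the previous score (log-odds 1 per SD). The effect is −0.29 at every follow-up visit and total loss is 10%. The complete-data effect in the same simulated sample is shown because it carries slight simulation noise.

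| True correlation | Mechanism | Complete data | Independence | Exchangeable | Unstructured |
|---|---|---|---|---|---|
| Exchangeable 0.5 | Same | −0.287 | −0.282 | −0.289 | −0.289 |
| | Control only | −0.288 | −0.233 | −0.289 | −0.288 |
| | Opposite | −0.302 | −0.206 | −0.301 | −0.300 |
| AR(1) 0.7 | Same | −0.289 | −0.281 | −0.291 | −0.290 |
| | Control only | −0.299 | −0.238 | −0.306 | −0.296 |
| | Opposite | −0.288 | −0.186 | −0.298 | −0.283 |

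**Size of bias at about 10% attrition.**

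- Same mechanism in both arms: at most about 0.01 SD (for example 0.289 − 0.281 = 0.008).
- Differing by arm, independence: from 0.288 − 0.233 = 0.055 to 0.29 − 0.146 = 0.144, so about 0.06 to 0.15 SD.
- Differing by arm, exchangeable: about zero when the true correlation is exchangeable. When it decays over time, from 0.306 − 0.299 = 0.007 to 0.29 − 0.257 = 0.033, so about 0.01 to 0.03 SD.
- Differing by arm, unstructured: within about 0.01 SD.

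**At 19% attrition (design B).** Control-only dropout under independence gives 0.284 − 0.178 = 0.106 SD of bias, and opposite mechanisms give up to 0.288 − 0.102 = 0.186 SD. Exchangeable stays within 0.308 − 0.288 = 0.020 SD and unstructured within 0.288 − 0.278 = 0.010 SD.

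**The case against.** Several counter-arguments carry weight.

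- **The sentence on retaining cases is literally true and concerns power.** A reader might infer that the authors regard GEE as having solved missing data. The text does not say so, and the separate step for missingness predictors suggests that they saw more was needed. That step does cover dropout explained by measured baseline variables.
- **Symptom-driven dropout does not by itself bias the interaction.** It must also act differently in the two arms, and the working correlation must be poor. Unstructured GEE does nearly as well as a likelihood model in the cases above.
- **A headline loss is not supported.** Control-only dropout under independence in design A gives (0.29 − 0.223)/0.29 = 23%, but the article never chooses an independence working correlation.
- **The direction is unknown.** Intervention activities take longer (30-60 against 20-30 minutes), and only that arm completes the Danger Assessment. That points, if anywhere, to the intervention arm, where symptom-driven dropout would exaggerate the effect. Repeating the activities at follow-up is optional and both arms complete the same measures, which weakens the case for differential dropout.
- **No post-randomisation covariate is named.** The rule permits one; it does not announce one.
- **Working correlation, imputation and sensitivity analyses commonly sit in the analysis plan.** Their absence from an article is not a finding, and none is claimed here.

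What remains is the adjustment rule that the article does state. It cannot do what is needed for dropout driven by follow-up scores, and it is not limited to baseline variables.

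**Conclusion.** The point holds in a conditional form. The stated handling of missing data is not guaranteed valid if dropout depends on earlier post-baseline scores, and the covariate rule as worded could admit variables affected by treatment. The documents do not show that the primary effect will be biased.

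At the planned attrition, the likely consequence ranges from negligible (about 0.01 SD with a common mechanism) through small (up to 0.03 SD with exchangeable correlation) to material (0.06 to 0.15 SD, in either direction, with independence and a mechanism that differs by arm). These figures rest on a true effect of 0.29 SD, assumed correlations of 0.5 to 0.7 and a log-odds of 1 per SD for dropout. They do not cover dropout that depends on unobserved scores, which no method above handles without a sensitivity analysis.

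This is worth changing because the change is cheap and uses the same data. It does not undermine the trial.

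**What to change.** 1. Analyse the primary outcomes with a likelihood-based repeated-measures model with unstructured covariance; a sandwich variance can be kept. Alternatively, keep GEE and run it on data multiply imputed separately by arm, with all earlier scores and the predictors of missingness in the imputation model.
2. State that covariates in the outcome model are baseline variables only. Post-randomisation predictors of missingness may enter the imputation model but not the outcome model.
3. Add a delta-shift sensitivity analysis by arm, for dropout that depends on unobserved scores.

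The cost is a few sentences in the analysis plan and modest programming. The downside is reliance on a correct covariance or imputation model. No new data are needed. The article gives the trial status as active follow-up, so the change could be dated and fixed before the arms are compared.
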